### Inclusion Criteria

Exposed group:

Children, adolescents, and young adults of the Nice region exposed by the terrorist attack and aged under 18 years on July 14^th^, 2016, according to DSM 5.Children of pregnant women at the time of the Nice attack.Affiliated to a social security scheme;Fluent in French;Informed written consent of legal guardians and child/adolescent.

Non-exposed group:

Children, adolescents and young adults, matched in age and gender to exposed group;Non-exposed to the “14–7” terrorist attack;Affiliated to a social security schemeFluent in French;Informed written consent of legal guardians and child/adolescent.

### Non-Inclusion and Exclusion Criteria

Non-inclusion criteria for the Nice cohort and control group were children, adolescents and/or young adults with average intellectual disability (IQ below 50), persons deprived of freedom after judicial or administrative decision, and persons subject to an exclusion period due to participation in other research.

Concerning the exclusion criteria, a request made by the child/adolescent/young adult or his/her parent for no longer participating to the “14–7” Program.

### Measures

Quantitative and qualitative measures are administered to the participants (summarized in **Table 1**):

Questionnaires regarding psychosocial risks (socio-demographic information; exposure to the traumatic event; care immediately after exposure; current care; social support, media exposure; legal procedure and assistance),Semi-structured interviews to assess the main diagnosis in children: MiniKid, Diagnostic Infant and Preschool Assessment (DIPA) or Kiddie—Schedule for Affective Disorders and Schizophrenia (K SADS),Salivary specimens for the construction of a biological DNA and RNA database,Clinical scales to assess PTSD: Young Child PTSD Checklist (YCPC), Child PTSD Checklist (CPC), or PTSD checklist (PCL),Clinical scales to assess anxiety: Preschool Anxiety Scale (PAS), Situational-Trait Anxiety Inventory for children (STAIC), or Situational-Trait Anxiety Inventory (STAI),Clinical scales to assess depression: Children’s Depression Rating Scale (CDRS) or Hamilton Depression Rating Scale (HDRS),Clinical scales to assess ADH/D (Conners),Clinical scales to assess dissociative experiences: Peri-traumatic Dissociation Experiences Questionnaire (PDEQ),Evaluation of social aspects: Brief Infant-Toddler Social and Emotional Assessment (BITSEA), Inventory of Parenting and Peer Attachment (IPPA), Kidscreen, parental stress index—short form (PSI-SF), or Post-Trauma Inventory of Parental Style (PIPS),Cognitive and socio-affective development for the youngest patients (Cognitive and Socio-Emotional Evaluation Battery: BECS) and intelligence quotient: Wechsler Preschool and Primary Scale of Intelligence (WPPSI), Wechsler Intelligence Scale for Children (WISC), or Wechsler Adult Intelligence Scale (WAIS).Parents’ clinical symptoms are also evaluated with the Clinical Global Impression (CGI), Clinical Global Assessment Scale (CGA), PCL, HDRS, STAI, PDEQ, PSI-SF and PIPS.

Clinical scales are all based on DSM-5 classification. They are scientifically validated assessment tools and are often used in clinical settings.

### Data Collection Process

Each investigator at the different study centers is responsible for collecting and entering data on the electronic CRF (Case Report Form) at the time of the visit. The Child and Adolescent Psychiatry University Unit (SUPEA) and the Research Center (Epidemiology and Population Health (INSERM U1018)) will perform data analysis of the database.

### Statistical Analysis

Statistical analyses will be run with R, SPSS, and AMOS softwares.

Descriptive analyses of all the parameters collected at baseline and during follow-up will be conducted.

Correlations will be carried out to examine associations between trauma history and exposition, sociodemographic, psychiatric, environmental, psychological and biological data.

Analyses of variance will be conducted to test the differences between the exposed group and the control group on trauma history and exposition, sociodemographic, psychiatric, environmental, psychological and biological data.

Multivariate models (linear and non-linear regression models, mediation and moderated mediation models) will be carried out to:

examine associations between clinical conditions (trauma history and exposition, sociodemographic, psychiatric, environmental, psychological, and biological data), at baseline in children and parents,predict clinical evolution over time with trauma history and exposition, sociodemographic, psychiatric, environmental, psychological and biological variables. Significant predictors from bivariate analysis (at p < 0.05) will then be included in a multivariate regression model. Owing to overlap of assessments, multicollinearity of predictors will be tested and addressed in multivariable models.

Each individual hypothesis will be tested at a significance level of 0.05. However, in order to compensate for the likelihood of incorrectly rejecting a null hypothesis when testing multiple hypotheses (i.e., making a Type I error), methods such as the Bonferroni correction will be used to reduce the likelihood of Type I error when testing multiple comparisons.

These statistics will be conducted on data from the whole cohort and from single groups (i.e., group of exposed children and non-exposed group) and on data from all collection waves.

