The primary objective of the “14–7” Program is to characterize the risk and/or protective psychosocial factors affecting the clinical evolution of a pediatric population sample exposed to the terrorist attack of July 14^th^, 2016 in Nice.

Secondary objectives of the “14–7” Program are to examine efficacy of clinical treatments as a function of the developmental age of the child, and to develop recommendations for treatments and therapies.

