## Participants

Two groups were defined:

Group 1: children exposed to the “14–7” terrorist attack;Group 2: children non-exposed to the “14–7” terrorist attack.

Patient selection and recruitment:

Exposed children are recruited by consultation registry of the Nice CHU Lenval, ORSAN database (a national list of victims from terrorist attack). Controls will be matched on age and sex. Moreover, participants will be recruited *via* press advertisements and National Education. For the control group, categorical screening criteria were used to estimate the number of subjects necessary to reach a statistical power of 80% with a risk of type-I error (α) of 5% for the main outcome variable. Assuming a frequency of development of PTSD of 20% in the general population, to demonstrate a 40% increase in incidence (incidence rate found during violent and intentional traumatic events), it is necessary to include 1,122 participants; that is, 561 child controls. We will then include 600 children (150 per centre) matched on age and sex to the group of exposed children.

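### Entering predictors of clinical evolution by uncorrected bivariate p < 0.05 can leave out known and masked determinants, and the final model's p-values and intervals ignore the selection

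*Protocol article*

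**What the plan says.** The main objective is to "characterize the risk and/or protective psychosocial factors affecting the clinical evolution of a pediatric population sample exposed" to the Nice attack (Background; repeated in substance under Objectives and Outcomes). The models that serve it are described in the protocol article under Statistical Analysis. They are to "predict clinical evolution over time with trauma history and exposition, sociodemographic, psychiatric, environmental, psychological and biological variables", and the next sentence gives the entry rule: "Significant predictors from bivariate analysis (at p < 0.05) will then be included in a multivariate regression model".

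Two safeguards follow. On correlated predictors: "Owing to overlap of assessments, multicollinearity of predictors will be tested and addressed in multivariable models". On multiplicity, the plan first says "Each individual hypothesis will be tested at a significance level of 0.05" and then that "methods such as the Bonferroni correction will be used to reduce the likelihood of Type I error when testing multiple comparisons". The family over which the correction is counted is not defined, and neither safeguard is tied to the screening step. The rule mentions no covariate that enters regardless of its bivariate result.

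The Background names several determinants from earlier research: age, sex, socioeconomic status, earlier trauma, degree of violence experienced, prior mental disorder, parental PTSD and social support.

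**The concern.** The entry rule is a method that the article chooses, so this is not a detail left to a fuller document. It raises three problems.

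- A bivariate p-value is a poor guide to a factor's place in an adjusted model. A factor whose effect is offset by a correlated one shows little association on its own and is not selected. A real but weak factor often misses 0.05 by chance.
- Determinants already known have to qualify again in this sample. Age matters most, because the Measures section uses different instruments at different ages, so age is tied to how the outcome is measured.
- Predictors that enter were chosen because their association was extreme in these data. Conventional p-values and intervals from the refitted model treat them as if they had been fixed in advance.

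The list of risk and protective factors is the programme's main product, and under Outcomes it is meant to help practitioners find children at high risk.

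**Working it through.** **Inputs.** From the article: the 0.05 threshold; 191 children included so far (Abstract); 561 calculated controls and 600 children planned (Participants). These sizes serve only as plausible n; the article does not state the n for this model. Not in the article, hence assumed: 40 candidates (30 in some runs), pairwise correlation 0 or 0.3, standardised predictors, linear regression.

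The article gives no figure for this analysis to reproduce. Its one design calculation, the sample size, concerns the exposed-versus-control comparison, and nothing below depends on it.

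**1. Masked factor.** Let y = 0.2·x1 − 0.4·x2 + error (SD 1), with correlation 0.5 between x1 and x2.
- Bivariate slope of x1: 0.2 + (−0.4 × 0.5) = 0, so x1 passes the screen only at the 5% chance rate.
- Adjusted, n = 600: standard error ≈ 1/√(600 × 0.75) = 0.047; z = 0.2/0.047 ≈ 4.2; power ≈ Φ(4.24 − 1.96) ≈ 0.99.
- Simulated: enters in 5% of runs; significant in 98.5% when both factors are modelled.

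The cancellation is exact by construction, so this is an extreme case.

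**2. Weak true factor.** With independent candidates, a true effect of 0.10 SD enters 27% of the time at n = 191 and 64% at n = 561.

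**3. Intervals after selection.** A null candidate that passed has a bivariate p-value below 0.05 by construction. If candidates are independent, refitting changes its t-value little, so its 95% interval usually excludes zero.
- 40 independent nulls: intervals of survivors cover zero 12–20% of the time.
- 40 nulls, correlation 0.3: about 71%.
- 30 candidates, correlation 0.3, five same-sign true effects of 0.10: coverage for true effects that entered is 98% (n = 191) and 95% (n = 600). About 13 and 23 of the 25 null candidates enter, so there is little selection left to distort.

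**4. Bonferroni, by family.** With 40 independent nulls, the number of survivors M is binomial(40, 0.05). Given M = m, each survivor's p-value is uniform on (0, 0.05), so it falls below 0.05/m with probability 1/m. This treats the refitted p-value as equal to the bivariate one.
- P(any false factor | m) = 1 − (1 − 1/m)^m, which is 1, 0.75, 0.704, 0.684 and 0.672 for m = 1 to 5, and about 0.66 beyond.
- P(M = m) = 0.271, 0.278, 0.185, 0.090 and 0.034 for m = 1 to 5, and 0.014 beyond.
- Sum: 0.271 + 0.208 + 0.130 + 0.062 + 0.023 + 0.009 ≈ 0.70.
- Over all 40: 1 − (1 − 0.05/40)^40 = 0.049.

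Simulated: 67–72% over survivors only (35–41% at correlation 0.3), against 4–5% over all 40. With 30 independent candidates, survivors only gave 65–66%.

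**5. Comparator: all 40 candidates in one unscreened model, each tested at 0.05.**

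| Quantity | Screened | Unscreened |
|---|---|---|
| Any false factor, all null, correlation 0 | 85–89% | 82–89% |
| Any false factor, all null, correlation 0.3 | 44–48% | 81–86% |
| Mean significant estimate, true effect 0.10, n = 191, correlation 0 | 0.187 | 0.208 |
| Same, n = 561 | 0.124 | 0.126 |

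**The case against.** **The screen does not create the false factors.** A reader might infer that it does, pointing to false-factor rates of 84–89% and to significant weak effects overstated 1.9-fold at n = 191 and 1.24-fold at n = 561. Step 5 shows otherwise. An unscreened model tested at 0.05 does about as badly with independent candidates and worse at correlation 0.3, and it overstates significant effects slightly more. Those figures reflect many tests at 0.05 and reporting by significance. This objection stands in full, and the figures are not evidence against the screen.

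**Multiplicity is addressed.** The plan commits to a correction and does not say that it is limited to predictors that entered. Counted over all candidates, it controls false factors. That stands as far as it goes: the survivors-only reading is possible but not stated. The correction would still not repair the intervals or bring back omitted factors.

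**Nothing says that other variables are shut out.** The text says that significant predictors are included. It does not say that none can be forced in, and it describes the named variables as risk factors, not confounders. So the plan does not establish that known determinants will be lost. It does make bivariate significance the only stated route into the model.

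**Independence is unrealistic.** The plan itself expects overlapping assessments, so the worst coverage figures belong to the less likely setting. This stands and is why the range matters.

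**Scope.** The rule belongs to the prediction models. No screen is stated for the baseline association or mediation models. That is correct, but predicting clinical evolution is the part that answers the main objective most directly.

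**Conclusion.** The concern holds in limited form. The entry rule can omit named determinants and masked factors, and the inference that follows it ignores the selection. The size depends on quantities that the article does not give. Undercoverage is severe with independent null candidates, moderate at correlation 0.3, and close to absent when correlated true effects carry most candidates into the model. The false-factor rate after Bonferroni depends on a family that is left open.

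The article does not mention confidence intervals; that part follows from the method. All percentages rest on an assumed 30 or 40 candidates and a linear model. The documents do not support the stronger reading that the screen itself manufactures false or inflated risk factors. This is a should-fix point: the rule bears on the main objective, but its harm varies with the setting and the fuller plan may narrow it.

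**What to change.** - Replace the p < 0.05 entry rule with a prespecified core set drawn from the Background: age, sex, socioeconomic status, earlier trauma, prior disorder, parental PTSD and social support. Enter it whatever the bivariate results.
- Where a core factor lies on a planned mediation path (parental PTSD may), handle it in the mediation models, so that the effect of interest is not adjusted away.
- State that the multiplicity correction counts every candidate predictor tested, not only those that enter the final model.
- Label any other predictor selected from the data as exploratory. Penalised regression with internal validation is one option for these, reported without conventional p-values.

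The cost is a change of wording and a little more analysis in R, which is already planned. No new data are needed, since the core variables are within the planned assessments. The price is fewer nominally significant factors and slightly wider intervals.

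### Bonferroni is the only multiplicity correction named as an example; naming Holm's step-down procedure would be a nearly free gain in power, not the repair of an error

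*Protocol article*

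**What the plan says.** All the relevant text is in the Statistical Analysis section of the protocol article. It sets the level: "Each individual hypothesis will be tested at a significance level of 0.05". It then gives the reason for a correction, "in order to compensate for the likelihood of incorrectly rejecting a null hypothesis when testing multiple hypotheses", and the means: "methods such as the Bonferroni correction will be used to reduce the likelihood of Type I error when testing multiple comparisons".

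The tests are spread over six domains. The comparisons of exposed and control children cover "trauma history and exposition, sociodemographic, psychiatric, environmental, psychological and biological data", and the same domains supply the correlations and the regression predictors. The analyses are to be run in the whole cohort, in each group separately, and on all waves. The article does not say how many tests this makes or how they are grouped.

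**The concern.** The main objective is to characterise risk and protective factors, in the plural. The Background section lists many already linked to PTSD, among them repeated trauma, sex, age, socioeconomic status, prior disorders and parental distress. Several effects may therefore be real at once. In that setting plain Bonferroni compares every p-value with the strictest threshold, 0.05/m, even after some hypotheses have been rejected. Holm relaxes the threshold after each rejection at the same family-wise error. If the named example is followed in its plain form, some real differences will be left undeclared that could have been declared without any weaker error guarantee.

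**Working it through.** **Inputs.** The level of 0.05 per hypothesis is from the Statistical Analysis section; its sidedness is not stated, and two-sided is assumed. The number of tests m, the number k of real effects and the power per test are not in the article. Assumed values: m = 10, 20 or 40; k from 20% to 100% of m; each real effect with mean z = 2.80 (1.96 + 0.84, that is 80% power at unadjusted 0.05) or z = 3.5 (94%).

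**No figure in the plan to reproduce.** The only calculation in the article is the sample size in the Participants section. It is set at "statistical power of 80% with a risk of type-I error (α) of 5% for the main outcome variable", for one outcome and without adjustment, so it does not depend on the correction method and is not used here.

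**Step 1: Bonferroni is valid.** For m independent true nulls, each tested at 0.05/m, the family-wise error is 1 − (1 − 0.05/m)^m. For m = 10 this is 1 − 0.995^10 = 0.0489; for m = 20 it is 1 − 0.9975^20 = 0.0488. Unadjusted, the figures are 1 − 0.95^10 = 0.401 and 1 − 0.95^20 = 0.642.

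**Step 2: Holm has the same guarantee.** Order the p-values. Compare the i-th smallest with 0.05/(m − i + 1) and stop at the first failure. Suppose m0 nulls are true. The first true null to be rejected falls at step m − m0 + 1 at the latest, so its p-value is at most 0.05/m0. The chance that any of the m0 true nulls has so small a p-value is at most m0 × 0.05/m0 = 0.05, whatever the dependence. Every Holm threshold is at least 0.05/m, so Holm rejects all that Bonferroni rejects. The first threshold is the same in both, so the chance of at least one rejection is identical.

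*Illustration with invented p-values, m = 10.* Let the four smallest be 0.001, 0.004, 0.006 and 0.008. The Holm thresholds are 0.05/10 = 0.0050, 0.05/9 = 0.0056, 0.05/8 = 0.0063 and 0.05/7 = 0.0071. Holm rejects three. Bonferroni, at 0.005 throughout, rejects two.

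**Step 3: size of the gain.** Bonferroni power per test is Φ(mean z − z for 0.05/m two-sided). For m = 10 this is Φ(2.80 − 2.81) = 0.498; for m = 20, Φ(2.80 − 3.02) = 0.412; for m = 40, Φ(2.80 − 3.23) = 0.335. Holm power was simulated with independent z-tests (20,000 to 100,000 families per setting). Entries are average power over the real effects, Bonferroni to Holm.

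| Tests (real) | 80% unadjusted | 94% unadjusted |
|---|---|---|
| 10 (2) | 0.498 to 0.505 | 0.753 to 0.761 |
| 20 (4) | 0.413 to 0.421 | 0.683 to 0.695 |
| 40 (8) | 0.336 to 0.342 | 0.607 to 0.620 |
| 10 (5) | 0.500 to 0.532 | 0.758 to 0.796 |
| 20 (10) | 0.414 to 0.442 | 0.683 to 0.725 |
| 40 (20) | 0.335 to 0.354 | 0.609 to 0.649 |
| 10 (8) | 0.499 to 0.569 | 0.756 to 0.839 |
| 20 (15) | 0.412 to 0.460 | 0.683 to 0.765 |
| 40 (30) | 0.335 to 0.369 | 0.607 to 0.682 |
| 10 (10) | 0.498 to 0.609 | 0.755 to 0.894 |
| 20 (20) | 0.412 to 0.494 | 0.683 to 0.844 |

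The gain is about 1 point with 20% real effects and 2 to 4 points with half. With 75 to 80% it is 5 to 8 points for 10 or 20 tests; for 40 tests it is 3 points at the smaller effect and about 8 at the larger. It is 8 to 16 points when all are real.

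**Step 4: correlated tests.** The article expects overlapping assessments, so the check was repeated with correlation 0.5. At 80% unadjusted power the gains hardly move: 10 tests with 2 real, 0.497 to 0.504; 10 with 5 real, 0.498 to 0.529; 20 with 10 real, 0.412 to 0.442.

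In every simulated family Holm rejected all that Bonferroni rejected. Its family-wise error stayed within 5%; for 10 independent tests with no real effect it was 0.0488 for both methods.

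**The case against.** The strongest reply is that the plan has not made the choice being improved on. Bonferroni appears as one example of an open class, and Holm, itself a stepwise Bonferroni procedure, is already permitted. This stands. A reader might infer that the plan commits itself to single-step Bonferroni, or that its error control is defective. The article says neither, and Bonferroni controls the family-wise error under any dependence.

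A reader might also infer that the open wording lets the method be picked once the p-values are known. The article does not support that: it is a condensed account, and the SAP or full protocol, not shown here, may fix the method and the families beforehand.

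Three further limits stand.
- With few real effects the gain is only about 1 point, and for the smallest p-value it is nil.
- The article does not say that the correction governs the regression coefficients. Predictors enter the multivariate model on an unadjusted bivariate screen at 0.05, so it is not shown that risk factors for clinical evolution would be missed.
- The definition of the families matters more than the method. In the 80% column, Bonferroni power falls from about 0.50 with 10 tests to about 0.34 with 40, a larger change than any Holm gain shown in that column.

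None of this removes the point that the one method named has an alternative that never rejects less, at the same error rate.

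**Conclusion.** The point holds as an optional improvement. No statement or figure in the article is wrong, and no error guarantee is broken. For tests alone, Holm is at least as powerful as Bonferroni under the same conditions, and it suits a study that looks for several factors. The ordering of the two methods is a mathematical fact. The size of the gain is not known from the article: the figures rest on an assumed number of tests, share of real effects and effect size, and on two-sided testing. They also presume that the correction is applied to the tests in question.

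**What to change.** In the Statistical Analysis section, replace the mention of Bonferroni as an example with a named rule: p-values will be adjusted by the Holm step-down procedure at a family-wise level of 0.05 within each pre-specified family of tests. The families should be listed in the SAP, if that is not already done, because the rule has no definite meaning without them.

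The cost is one sentence and one software option in R, which the plan already names. There is no loss for the tests. The one downside concerns intervals: simultaneous confidence intervals would still use Bonferroni widths, so an interval may include the null value for a hypothesis that Holm rejects. If such intervals are reported, the text should say so.
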